This technique consists of creating the pneumoperitoneum, which is the insufflation of a gas through a small incision in the abdominal wall in order to separate it from Organs internal organs, allowing a better visibility of the area to be treated by the surgeon and manipulation of the instruments within the cavity. (BIRCH DW, DANG JT, SWITZER NJ, MANOUCHEHRI N, SHI X, HADI G 2016).

The pneumoperitoneum pressure is defined as normal and adequate when the values ​​are between 12 to 15 mmHg, being considered low when the values ​​are between 5 to 7 mmHg, below this last band it would be practically impossible to practice this surgical technique, because the visualization of structures would be greatly impaired (NEUDECKER et al. 2002). The increase in this pressure leads to an increase in gas absorption, elevates the diaphragm, decreasing lung compliance and increasing airway pressure. Increased intra-abdominal pressure increases venous return due to compression of the splanchnic vasculature. Pneumoperitoneum also increases systemic vascular resistance and pulmonary vascular resistance. During the initial phase of the pneumoperitoneum, cardiac output is reduced by decreasing venous return. Although these changes are well tolerated by healthy individuals with a good cardiopulmonary reserve, patients without this reserve may not tolerate as well (GURUSAMY KS, VAUGHAN J 2014). Approximately 17% of patients undergoing laparoscopic cholecystectomy are ASA III or IV (GIGER et al. 2006), whereas in oncological surgeries this number may be even higher.

The ideal gas would be one with the following properties: minimum peritoneal absorption, minimum physiological effects, rapid excretion of any absorbed gas, non-oxidizing, minimal effect of intravascular embolization and high blood solubility (GERGES et al. 2006).

Among the available gases, the most commonly used is carbon dioxide because it has characteristics closer to the ideal gas, but it also has undesired characteristics (GERGES et al. 2006). Due to its diffusibility characteristic, the pneumoperitoneal caused by carbon dioxide is dissolved quickly, however despite the speed, a certain amount can remain and cause discomfort. Due to its high solubility it can cause hypercarbia, hypercapnia and acidosis (MENES and SPIVAK 2000).

As soon as pneumoperitoneum is established, there is an increase in intra-abdominal pressure and, consequently, cardiovascular, respiratory and neurological effects (CONACHER et al. 2004; HENNY and HOFLAND 2005; GERGES et al. 2006; KALMAR et al. 2010).

The severity of possible cardiovascular effects such as blood pressure variation, arrhythmias and cardiac arrest are related to the volume of carbon dioxide absorbed, the patient's intravascular volume, ventilatory technique, surgical conditions, anesthetic agents used, however the most important factors are intra pressure -abdominal and position of the patient (HENNY and HOFLAND 2005; GERGES et al. 2006).

Respiratory effects include reduced lung volume, increased airway pressure, decreased pulmonary compliance secondary to increased intra-abdominal pressure and patient position (CONACHER et al. 2004; HENNY and HOFLAND 2005; GERGES et al. 2006; KALMAR et al. 2010).

Neurological changes arise due to increased intracranial pressure, decreased cerebral perfusion, hypercapnia and increased systemic vascular resistance (CONACHER et al. 2004; GERGES et al. 2006; KALMAR et al. 2010).

Regarding the positioning of the patient for laparoscopic surgeries, the most diverse are described, but one of the most challenging and with the most physiological changes occurs in those that need to be performed in the Trendelenburg position (MARTIN JT 1997).

Headache or better known as Trendelenburg position was described in the middle of the 19th century, by a German surgeon Friedrich Trendelenburg, and continues to be used routinely today, mainly in surgeries of the genitourinary or colorectal tracts. One of the great advantages of using this position is the improvement of the exposure of the surgical field providing the improvement of the surgical technique (MARTIN 1997; TALAB et al. 2016). Patients with prolonged duration in this position may have edema of the face, conjunctiva, larynx and tongue with a potential risk of airway obstruction. Special care must also be taken with the patient's positioning, as he becomes subject to a nervous plexus injury (ANDREA CESTARI and MARIA BUFFI, EMANUELE SCAPATICCI, GIOVANNI LUGHEZZANI, ANDREA SALONIA, ALBERTO BRIGANTI, PATRIZIO RIGATTI, FRANCESCO MONTORSI) (MICHEL W. COPPIETERS 2002).

Some disadvantages of this procedure associated with the Trendelenburg position would be pulmonary pathophysiological changes with the formation of atelectasis and increased airway pressure. They are also associated with increased intracranial pressure and the formation of cerebral edema. These effects could lead to low cerebral perfusion and potential mismatch of oxygen supply to the brain (CONACHER et al. 2004; CLOSHEN et al. 2014; ROSENDAL et al. 2014).

For laparoscopic surgeries, general anesthesia with short-term agents is almost unanimous. With regard to the technique for maintaining general anesthesia, there are currently two techniques: total intravenous anesthesia and inhalation anesthesia. Both are universally used, with rare exceptions for one technique to be more advantageous compared to the other technique, as in certain specific situations. Total intravenous anesthesia would be better indicated for patients with a history of nausea / vomiting in the postoperative period (APFEL et al. 2002; LEE et al. 2015), it is not a triggering agent of malignant hyperthermia (HOPKINS 2000; MANI and MORTON 2010) less disorders of behavior in the postoperative period of pediatric surgery (ORTIZ et al. 2014), anesthesia in neurosurgery with a tendency to intracranial hypertension (PETERSEN et al. 2003). Inhalation anesthesia would be more beneficial with neuroprotection (KITANO et al. 2007), cardioprotection (FRABDORF et al. 2009; PS 2010) and less chance of intraoperative recall (AMERICAN SOCIETY OF ANESTHESIOLOGISTS TASK FORCE ON INTRAOPERATIVE AWARENESS 2006).

The association with spinal anesthesia, provided that the guidelines for its contraindications are followed (TABLE 1), is also seen as advantageous, since it produces earlier awakening, reduces nausea and vomiting, postoperative pain, length of hospital stay, effective cost, improvement patient satisfaction (BESSA et al. 2012; CARD et al. 2015; DAY et al. 2015; GERGES et al. 2006; GHOSH et al. 2015; SINHA et al. 2009; WONGYINGSINN et al. 2012) and mainly the decrease consumption of anesthetic agents for general anesthesia (GERGES et al. 2006).

Chart 1 - Contraindications to spinal anesthesia.

| Absolute | Relative |
| --- | --- |
| Patient refusal | Coagulopathy |
| Significant hypovolemia | Sepsis / bacteremia |
| Infection at the puncture site | Previous neurological disease |
| Intracranial hypertension | Peripheral neuropathy |
| Significant coagulopathy | Multiple sclerosis |
|  | Demyelinating process |

As a disadvantage, when associating the two anesthetic techniques, patients become susceptible to the adverse events inherent to spinal anesthesia. Among these, the most common are hypotension of around 5% (CARPENTER, RL; CAPLAN, RA; BROWN 1992; HARTMANN et al. 2002),

nausea and vomiting described in 15% (BORGEAT et al. 2003), pruritus varies from 30 to 100% of patients (RATHMELL et al. 2005), urinary retention was observed in up to 35% of patients (KUIPERS et al. 2004), tremors, which can occur in up to 50% of patients (CROWLEY and BUGGY 2008) (CROWLEY and BUGGY 2008). Intrinsic complications to the procedure are rare, but described in the literature, such as hematoma, infection, and fatal cardiovascular glue in 1 / 100,000 patients (COOK et al. 2009; MOEN et al. 2004).

Another possibility would be spinal anesthesia with opioids alone, more commonly morphine (ARAIMO MORSELLI et al. 2016; DICHTWALD et al. 2016), bringing the benefit of analgesia for a period of 12 to 24 hours, without the cardiovascular consequences caused by the blockade sympathetic as a consequence of using the local anesthetic (ARAIMO MORSELLI et al. 2016).

Currently, in laparoscopic surgeries, it is not clear which is the best anesthetic technique for such a procedure. There are attempts to search for indications of spinal anesthesia through systematic literature reviews (PROSPECT [s.d.]) or guidelines (AMERICAN SOCIETY OF ANESTHESIOLOGISTS TASK FORCE ON ACUTE PAIN MANAGEMENT 2012), however none is categorical and with a strong level of evidence in affirming such conduct.

In the postoperative period, one of the most feared neurological changes is delirium, being considered the most common post-surgical complication, occurring between 5 to 50% of the procedures (INOUYE et al. 2014). The same is a perverse and complicated process that brings countless challenges to the team that accompanies the patient (ALDECOA et al. 2017; STEINER 2011a). Especially harmful in the elderly, since a single episode can trigger a cascade of events such as: prolonged hospitalization, loss of functional independence, reduction of cognitive function and death (SACZYNSKI JS, MARCANTONIO ER, QUACH L, FONG TG, GROSS A, INOUYE SK 2012). Some meta-analyzes suggest that a single episode of delirium increases the risk of death by 2 times, increases the time of mechanical ventilation, time in the ICU and hospital stay (MCDANIEL and BRUNEY 2012).

Delirium is defined in the DSM V (Diagnostic and Statiscal Manual of Mental Disorders) as: disturbance of consciousness, alteration of cognition and acute and fluctuating course time (AMERICAN PSYCHIATRIC ASSOCIATION 2013).

Clinically, there are several methods for diagnosing delirium, but the most widely used is performed using the Confusion Assemenment Method (CAM) (FABBRI et al. 2001; STEINER 2011b) (ANNEX 1), a simple screening method based on four questions that it has a sensitivity of 86% and a specificity of 93% (WONG et al. 2010). The checklist for diagnosing delirium consists of 4 items: 1 - Acute onset; 2- Attention disorder; 3- Disorganized thinking; 4 - Change in the level of consciousness. The diagnosis of delirium requires the presence of criteria 1 and 2 plus criteria 3 or 4.

A variant known as CAM-ICU is often used in intubated or sedated patients (ELY et al. 2001; LUETZ et al. 2010), but at present there is still no specific and well-established method for evaluating the delirium of surgical patients in immediate postoperative period.

There are 3 subtypes of delirium: hyperactive (agitation and restlessness) (25%), hypoactive (lethargy and inattention) (50%) and mixed (25%). In a study involving 400 patients, with a median age of 57 (44.67) years, evaluated in the anesthetic recovery room, 124 (31%) had delirium on admission to the anesthetic recovery room, 59 (15%) 30 minutes after admission, 32 (8%) with 60 minutes after admission and 15 (4%) at discharge from the anesthetic recovery room. In patients with signs of delirium, hypoactive signs were present in 56% on admission to the anesthetic recovery room and in 92% during their stay in the anesthetic recovery room (CARD et al. 2015). The hypoactive subtype is the most prevalent and also associated with higher mortality. Although there is no consensus on the definition of postoperative delirium, most studies define its occurrence between 24 to 72 hours postoperatively, however some still occur after discharge from hospital (WHITLOCK et al. 2011; CARD et al. 2015).

The Richmond Agitation Sedation Scale (RASS) scale, developed with the objective of characterizing the level of consciousness and agitation, is routinely used in association with CAM to characterize delirium. Signs of hyperactive delirium are defined with a RASS score ranging from +1 (anxious patient) to +4 (agitated patient) accompanied by positive CAM. Signs of hypoactive delirium will be defined as RASS ranging from - 5 (patient does not respond) to 0 (calm or sleepy patient) accompanied by negative CAM (NASSAR et al. 2008; SESSLER et al. 2002) (ANNEX 2).

Currently, the most accepted hypothesis for the pathophysiology of delirium in the postoperative period seems to be an acute neurological insult in a patient with a susceptible substrate. Such a disjunction results from an alteration in the balance of neurotransmitters or neuroinflammatory mediators in the brain, resulting in clinical symptoms of delirium. The most commonly affected pathways include acetylcholine, dopamine, gamma aminobutyric acid (GABA) and serotonin, where the most common neuroinflammatory marker involves the hypothalamic pituitary axis, represented by cortisol, as well as C-reactive protein (CRP), pro calcitonin, tumor necrosis and various interleukins such as IL-6, IL-8 and IL-10 (ALI et al. 2011). Although there is general acceptance of which clinical indicators define the susceptible substrate, there has been an increase in efforts to identify preoperative and postoperative biochemical markers that may help to identify potential risks for delirium based on the aforementioned theories (MCDANIEL and BRUNEY 2012) .

The assumed risk factors are multifactorial and these can be grouped into non-modifiable and modifiable. In the first group there is an increase in age, a poor functional status already detected in the preoperative period, comorbidities (dementia, depression, nephropathy, heart disease and lung diseases), type of surgery (emergency, orthopedics, cardiovascular) (SCHOEN et al. 2011 ). The second group includes certain classes of drugs (opioid, benzodiazepine, antihistamine, dihydropyridine) (CLEGG and YOUNG 2011), polypharmacy (more than six drugs or the addition of three new ones), infection or inflammation, pain, electrolyte disturbance ( sodium and potassium), hematological changes (anemia, hypoxemia), changes in the sleep-wake cycle (WHITLOCK et al. 2011; SANDERS et al. 2011; CHAPUT and BRYSON 2012), pressure of intraoperative erfusion and possibly depth of the anesthetic plan (SIEBER et al. 2010).

Regarding the use of drugs, opioids should be prescribed with caution, since their use, especially in high doses, could increase the risk of delirium. On the other hand, severe pain not properly treated is associated with its appearance. Regarding benzodiazepines, the association occurs mainly with high doses and with long-lasting drugs (CLEGG and YOUNG 2011).

It is common knowledge that a preoperative assessment and identification of risk factors greatly reduces the chances of the event (ADULTS 2014).

One of the ways found to try to reduce the incidence of delirium during the operation is through the modernization of monitoring. Regarding multimodal monitoring (cardiac output, depth of hypnosis, cerebral oxygenation), this has been gaining a lot of focus. By detecting and reducing complications, it contributes to videolaparoscopy to come closer to the ideal surgery method (GREEN et al. 2014).

Neuromonitoring during anesthetic procedure can improve the patient's awakening (GUARRACINO 2008; FEDOROW and GROCOTT 2010). The BIS (Bi-Spectral Index) is derived from an analysis of the electroencephalogram (EEG) and represents the anesthetic depth through a single value that can vary from 0 to 100 and that correlates with sedation and hypnosis, being used clinically for anesthetic agents. Values ​​between 40 and 60 are said to be suitable for surgery (AG et al. 2016). It was one of the first EEG indices and became one of the most used monitors for this purpose in the world. Through it, it is possible to perform hypnosis at the appropriate levels to perform the procedure (PUNJASAWADWONG et al. 2010; KLOPMAN and SEBEL 2011). BIS-guided hypnosis could influence cognitive level and postoperative mortality (FARAG et al. 2006; MONK et al. 2005), however it is still controversial (KERTAI et al. 2011; LESLIE and SHORT 2011).

Today much is said about Triple Low, where patients with low Bispectral Index Scores (BIS) with low concentration of anesthetic agents associated with low perfusion pressure have high rates of morbidity and mortality in 30 to 90 days (DEINERSTACIEANDJEFFREYH.2013).

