Subsequent general anesthesia with pre-oxygenation 8 liters / minute for 5 minutes + fentanyl 3 mcg / kg + propofol 2 mg / kg + rocuronium 0.6 mg / kg will be performed. Anesthesia will be maintained with remifentanil (mcg / kg / min) and desflurane (Fe%).

Hypnosis will be guided by keeping BIS between 40 and 60 and the remifentanil dose will be guided by vital signs.

In both groups, patients will be kept warm with a thermal blanket and their esophageal temperature measured (distance of 40 cm from the incisor teeth) (DANIEI 2008; WANG 2016).

The following parameters will be measured: heart rate, blood pressure, BIS, capnography, saturation, TOF, esophageal temperature and Trendelenburg angle.

The measured moments will be the patient's entry into the operating room, after pre- anesthetic medication, pre-anesthetic induction, after anesthetic induction, after surgical incision, after pneumoperitoneum inflation, after Trendelenburg position, every 15 minutes until the end of the procedure. after extubation.

After the surgical procedure is completed and 5 minutes after extubation, vital signs (blood pressure, heart rate, saturation) will be collected and the patient will be evaluated for delirium. Dipyrone 2 grams and parecoxib 40 mg will be performed with no contraindication for postoperative analgesia.

Afterwards, patients will be referred to the anesthetic recovery room (PACU), where they will continue to be monitored with ECG, noninvasive pressure and pulse oximeters. They will also be evaluated for pain on the numerical rating scale (NRS) (0 = no pain, up to 10 = worst pain), on arrival and every 30 minutes until discharge to the room. Those with NRS> 4 on the PACU will be treated with morphine 1 mg every 10 min or NRS <4. Those with nausea / vomiting will be treated with alizapride 50 mg.

Patients will be assessed for delirium onset using the Confusion Assemenment Method (CAM) (SUPPLEMENT1) in combination with the Richmond Agitation Sedation Scale (RASS) scale (SUPPLEMENT 2).

This evaluation will be performed by nurses, previously trained, upon arrival at the PACU, every 30 minutes until discharge from the post-anesthetic recovery room and every 24 hours until discharge, by the researcher himself. If the patient has an episode of delirium that persists for more than 1 hour, a psychiatrist will be asked for follow-up and treatment.

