**Criteria 1 and 2 plus 3 or 4 must be present.**

Adapted from: (INOUYE SK, VAN DICK CH, ALESSI CA 1990)

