**SUPPLEMENT 2 - Richmond Agitation Sedation Scale - RASS Richmond Agitation Sedation Scale - RASS**

| **Score** | **Term** | **Description** |
| --- | --- | --- |
| + 4 | Combative | Overtly combative or violent; immediate danger to staff |
| + 3 | Very agitation | Pulls on or removes tube(s) or catheter(s) or has aggressive behavior toward staff |
| + 2 | Agitated | Frequent nonpurposeful movement or patient–ventilator dyssynchrony |
| + 1 | Restless | Anxious or apprehensive but movements not aggressive or vigorous |
| 0 | Alert and calm |  |
| - 1 | Drowsy | Not fully alert, but has sustained (more than 10 seconds) awakening, with eye contact, to voice |
| - 2 | Light sedation | Briefly (less than 10 seconds) awakens with eye contact to voice |
| - 3 | Moderate sedation | Any movement (but no eye contact) to voice |
| - 4 | Deep sedation | No response to voice, but any movement to physical stimulation |
| - 5 | Unarousable | No response to voice or physical stimulation |

Source: Adapted from: (SESSLER et al. 2002).

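### The Introduction defines hypoactive delirium by a negative CAM, against the protocol's own CAM rule, and this is the only text saying how CAM and RASS combine

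*Protocol*

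**What the plan says.** Four places in the protocol bear on how delirium is scored.

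- **Introduction, paragraph on CAM.** "The diagnosis of delirium requires the presence of criteria 1 and 2 plus criteria 3 or 4". The next paragraphs name hyperactive, hypoactive and mixed subtypes and characterise the hypoactive patient as lethargic and inattentive.
- **Introduction, paragraph on RASS.** The hyperactive type is RASS +1 "to +4 (agitated patient) accompanied by positive CAM". For the other type: "Signs of hypoactive delirium will be defined as RASS ranging from - 5 (patient does not respond"), continuing "to 0 (calm or sleepy patient) accompanied by negative CAM".
- **Material and Methods.** "Patients will be assessed for delirium onset using the Confusion Assemenment Method (CAM"), "in combination with the Richmond Agitation Sedation Scale (RASS) scale", with pointers to Supplements 1 and 2. No rule for combining the two is given there.
- **Supplements.** Supplement 1 ends its four-item checklist with "Criteria 1 and 2 plus 3 or 4 must be present". Supplement 2 describes RASS 0 as "Alert and calm".

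The incidence of delirium is the only objective in section 3. The statistical paragraph analyses it as a binary outcome, delirium or not.

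**The concern.** The two subtype definitions in the Introduction take opposite CAM results. A type of delirium that requires a negative CAM cannot coexist with a rule under which every delirium diagnosis needs a positive one. Because Methods uses both scales and does not say how, a rater or trainer looking for the combining rule finds it only in that Introduction sentence, which is worded as something that will be done.

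The trial's single outcome depends on this classification. It is scored by trained nurses in the recovery room and by the researcher every 24 hours until discharge. If the raters work from different sentences, they may classify the same patient differently.

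**Working it through.** **1. The passages side by side.** Crossing CAM result with RASS range gives four cells.

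| CAM | RASS | Introduction, RASS paragraph | Introduction CAM rule and Supplement 1 |
| --- | --- | --- | --- |
| positive | +1 to +4 | hyperactive delirium | delirium |
| positive | -5 to 0 | no subtype | delirium |
| negative | -5 to 0 | hypoactive delirium | not delirium |
| negative | +1 to +4 | not delirium | not delirium |

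The two readings disagree outright in the third row. That row includes RASS 0, which Supplement 2 reserves for the alert, calm patient and the Introduction glosses as possibly sleepy. In the second row the patient is a case under Supplement 1 but fits neither written subtype. The mixed type has no CAM/RASS rule that could take this patient in.

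The Introduction's own description of the hypoactive patient points the same way. Inattention is CAM criterion 2 and lethargy is an example under criterion 4. With acute onset (criterion 1), that patient is CAM-positive.

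**2. The plan's own figure.** The inputs are 5% versus 21%, one-sided 5% level, 85% power and 62 per group. With pooled variance and no continuity correction:

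n = [1.645 × √(2 × 0.13 × 0.87) + 1.036 × √(0.05 × 0.95 + 0.21 × 0.79)]² / 0.16² ≈ 62.1 per group

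This is 63 if rounded up. Power at 62 per group is 84.9%. The stated size is reproduced, and it rests on CAM-type delirium rates.

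**3. Effect if the RASS paragraph were applied literally.** Let p be the CAM-positive rate (5% exposed, 21% not exposed). Let h be the share of CAM-positive patients with RASS 0 or below, and q the same share among CAM-negative patients.

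- h = 0.50 to 0.92. The Introduction gives hypoactive as 50% of delirium, 56% of those with signs at recovery-room admission and 92% during the stay. Using these for h is an approximation.
- q = 0.80 to 0.95. This is an assumption; the protocol gives no figure.

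Labelled rate = p(1 − h) + (1 − p)q

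| h | q | Exposed | Not exposed | Difference (not exposed − exposed) |
| --- | --- | --- | --- | --- |
| 0.50 | 0.80 | 0.025 + 0.760 = 78.5% | 0.105 + 0.632 = 73.7% | -4.8 points |
| 0.50 | 0.95 | 0.025 + 0.9025 = 92.8% | 0.105 + 0.7505 = 85.6% | -7.2 points |
| 0.92 | 0.80 | 0.004 + 0.760 = 76.4% | 0.0168 + 0.632 = 64.9% | -11.5 points |
| 0.92 | 0.95 | 0.004 + 0.9025 = 90.7% | 0.0168 + 0.7505 = 76.7% | -13.9 points |

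The planned difference is +16 points. Algebraically the literal difference is 0.16 × (1 − h − q), so the sign reverses whenever h + q exceeds 1. It does so throughout the ranges shown.

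**The case against.** The strongest reply is that Methods sends the rater to the two supplements and not to the Introduction. Supplement 1 carries the correct case rule. The analysed outcome is binary and no subtype analysis is described. A nurse who fills in Supplement 1 and applies its closing rule therefore classifies every patient correctly. The Introduction sentence sits among cited background and speaks of signs of a subtype. The text has other translation slips, so one wrong word is a likely explanation. The planned rates of 5% and 21% also show that nobody meant to count normal recoveries as cases.

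Most of this stands, and it limits the finding. A reader might infer that the primary outcome is inverted, so that most of the 79-95% of patients expected to be free of delirium would count as cases. The protocol does not support that: it would need the Introduction sentence to override Supplement 1, and it would need a share of CAM-negative patients at RASS 0 or below that is nowhere given. Nor are the CAM-positive, drowsy patients lost as cases; what they lack is a subtype label.

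A reader might also fault CAM item 4 for naming only depressed states of consciousness. The item offers them as examples, so agitated states are not excluded.

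The reply does not remove the contradiction. Nothing in the protocol corrects the sentence, and Methods invokes a combination of scales that only this sentence spells out.

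**Conclusion.** The point holds as an internal contradiction in the outcome definition. The hypoactive definition conflicts with the CAM rule in the Introduction and Supplement 1, with the Introduction's description of that type, and with Supplement 2 on the meaning of RASS 0. The subtype definition is wrong whichever way raters work.

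Harm to the binary outcome is conditional: it arises only if a rater applies the Introduction's RASS paragraph. In that case, under the assumed 80-95% and the approximate 50-92%, the labelled rates would be about 76-93% (exposed) and 65-86% (not exposed), and the planned difference would reverse by roughly 5 to 14 points. These figures show what is at stake; they do not predict what the trial will record. The sample size is not in question here.

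**What to change.** - In Material and Methods, state that the binary outcome is CAM-positive delirium as in Supplement 1 (criteria 1 and 2, plus 3 or 4), and that RASS only describes the subtype among CAM-positive patients.
- In the Introduction's RASS paragraph, change the CAM result for the hypoactive type from negative to positive.
- Align the Introduction's gloss of RASS 0 with Supplement 2.

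No new scoring rule for CAM item 4 and no new RASS cut-offs are needed to resolve the contradiction. The cost is a few words in the protocol and a line in the nurse training, with no extra assessments and no change to the sample size. The protocol describes the project as in progress, so if patients have already been assessed, confirm which rule the raters followed.
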